### Statistical analysis

Descriptive statistics will be used for continuous variables, and frequencies for categorical variables. The “last observation carried forward” (LOCF) principle will be used to compensate for missing data. The LOCF principle involves replacement of missing data with the last observed value to obtain a complete database.

When the assumption of normality is satisfied will a *t*-test be used to compare the two groups in terms of the primary outcome (mean cough diary score at week 4). Otherwise, the Mann–Whitney *U*-test will be used. Other continuous variables, such as mean efficacy measurements (cough VAS score or LCQ scores), safety tests (AST, ALT, ALP, TB, GGT, BUN, creatinine, sodium or potassium levels), and biomarkers will be analyzed using the same statistical methods. Associations between the MMDT responders and non-responders with regard to each identified pattern will be estimated using a logistic regression model, which will be adjusted for covariates. All data will be analyzed using SPSS™ for Windows software. The level of significance will be set at a two-sided P value of 0.05.

We, along with a professional statistician, will perform the data analysis for the results.

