#### Placebo

The control group will receive placebo granules (3 g/pouch, 3 times per day—before each meal—for 4 weeks). The placebo was manufactured by the Jeonnam Bioindustry Foundation Food Research Center (JBF), following the placebo guidelines of the Korean Ministry of Food and Drug Safety. The granules do not contain any active ingredients, but are similar in appearance, taste, and scent to the MMDT granules.

All products were packaged by JBF (Naju, Republic of Korea). Either Forty-two MMDT or placebo pouches will be provided to each randomized participant at visit 1 (week 0 ± 3 days) and visit 2 (week 2 ± 3 days). The products will be stored at the K-CTC clinical research pharmacy in Kyunghee University Korean Medicine Hospital, and an independent and trained pharmacist will manage all procedures associated with the drugs. The study process is outlined in Table 1.

**Table 1 Tab1:** Study process: treatment and outcome measurements

Activity	Screening	Visit 1	Visit 2	Visit 3	Follow up
Time schedule	-Week 1	Baseline	Week 2	Week 4	Week 6
Window visit		±3 days	±3 days	±3 days	±3 days
Informed consent	X				
Demographics	X				
Cough symptom check	X				
Medical history	X				
Smoking history	X				
Medication history	X				
Safety test	X	X		X	
Chest X-ray	X				
Pulmonary function test	X				
Safety test	X				
Methacholine bronchial challenge test^a^	X				
Nasal endoscopy^a^	X				
Distribute cough diary card	X	X	X	X	
Randomization		X			
Height/weight/body mass index		X			
Vital sign		X			
Cough diary score		X	X	X	X
Cough visual analogue score		X	X	X	X
Leicester cough ques-tionnaire Korean versi- on		X		X	X
Pattern identification for chronic cough question-naire		X		X	
Cold-Heat pattern questionnaire		X		X	
Yin deficiency scale		X		X	
Hematological biomarker		X		X	
Immunologic biomarkers		X		X	
Investigational Produce		X	X		
Compliance			X	X	
Adverse events investi-gation			X	X	
Concomitant therapy eva- luation	X	X	X	X	

^a^The test will be performed as needed, according to the judgment of the investigator

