### Outcome measures

#### Primary outcomes

The primary outcome is the cough diary score at week 4. The cough diary score on the last day of the 1-week run-in period will be taken as the baseline score of participants who will be enrolled and randomized for the trial.

The cough symptom scoring recommended by Spector et al. will be used in this study [27]. The daily cough diary consists of two parts: daytime (08:00–20:00) and nighttime (20:00–08:00) cough symptoms. Patients will be required to evaluate their symptoms twice per day (daytime and nighttime). Daytime cough symptoms will be graded from zero to five as follows: 0—no cough; 1—cough for one short period; 2—cough for two or more short periods; 3—frequent coughs that did not interfere with usual daytime activities; 4—frequent coughs that did interfere with usual daytime activities; and 5—distressing coughs for most of the day. Nighttime cough symptoms will be graded from zero to five as follows: 0—no cough during the night; 1—cough on waking only; 2—waking once or early precisely because of cough; 3—waking frequently due to cough; 4—wakefulness for most of the night due to cough; and 5—distressing coughs preventing sleep. The total cough score (from 0 to 10) is the sum of the daytime and nighttime cough symptom scores.

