### Sample size calculation

We referred a randomized controlled trial (RCT) that was conducted to demonstrate the clinical efficacy of a herbal medication for the patients with cough variant asthma (CVA) [36]. It was inevitable because no RCTs have been carried out that address the comprehensive chronic cough symptom using a herbal mediation. Furthermore, the main manifestation of CVA is cough lasting more than 8 weeks without any abnormal pulmonary functions; this is very similar to clinical characteristics of the eligible participants recruited in this study.

Using a cough diary score, the CVA study compared the efficacy of a herbal medicine with that of standard therapy (leukotriene receptor antagonist combined with methylxanthine) for 2 weeks. The calculated effect size was 0.699 (α = 0.05, 1-β = 0.8, 2-tailed test). Because of the discrepancy in comparators and study duration between the previous and planned studies, we determined to eliminate the effect of standard therapy and add the effect of longer treatment duration; this resulted in an adjusted effect size of 0.85. Assuming a 20 % dropout rate, and an allocation ratio of 1, we have calculated the necessary sample size to be 58 participants (29 in each group). The above calculations were performed using G*Power™ software (ver. 3.1.9.2) for Mac.

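### LOCF is the only missing-data method the article names, for all variables: it can distort the week-4 cough comparison and dilutes mean laboratory comparisons

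*Protocol article*

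**What the plan says.** The Statistical analysis section states: "The “last observation carried forward” (LOCF) principle will be used to compensate for missing data". It then explains: "The LOCF principle involves replacement of missing data with the last observed value to obtain a complete database". Neither sentence is limited to efficacy variables, and the article names no other way of handling missing data.

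Under Primary outcomes: "The primary outcome is the cough diary score at week 4". The planned comparison is a single-time-point test, "a *t*-test be used to compare the two groups in terms of the primary outcome (mean cough diary score at week 4", with the Mann–Whitney test if normality fails. The same section adds: "safety tests (AST, ALT, ALP, TB, GGT, BUN, creatinine, sodium or potassium levels), and biomarkers will be analyzed using the same statistical methods".

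Four other places bear on the point:
- **Sample size calculation.** After allowing for 20 % dropout: "dropout rate, and an allocation ratio of 1, we have calculated the necessary sample size to be 58 participants", that is 29 per arm. The effect size was raised from 0.699 to 0.85, partly because treatment lasts longer than in the 2-week reference study.
- **Intent-to-treat population.** One dose and one day of diary recordings are enough for inclusion.
- **Withdrawal criteria.** These include forbidden cough medication, under 80 % of doses, and a serious adverse event.
- **Table 1** ("Study process: treatment and outcome measurements"). Safety tests fall at screening, visit 1 and week 4. LCQ-K, PICCQ and biomarkers are measured at baseline and week 4, and LCQ-K again at week 6. None of these has an on-treatment value before week 4.

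**The concern.** LOCF assumes that a participant's score stays where it was when they left. The plan assumes otherwise: its hypothesis is that four weeks of treatment ease cough, and its effect size was increased because four weeks should achieve more than two. A diary score from the first days can nevertheless enter the primary analysis as the week-4 result.

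Several withdrawal reasons are plausibly related to cough control or tolerability, so dropout may be neither random nor equal between arms. If it is unequal, part of the measured difference would reflect who left and when.

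For variables first measured on treatment at week 4, carrying forward means recording no change since baseline. For liver, renal and electrolyte values, that pulls the between-arm comparison of means towards no difference. Efficacy and safety together are the trial's stated objective.

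**Working it through.** **1. The plan's own figure.** For d = 0.85, two-sided α = 0.05 and power 0.80, the noncentral t calculation gives 22.73, so 23 per arm (power 80.5 %). Then 23 / (1 − 0.20) = 28.75, rounded up to 29 per arm, or 58 in total. The stated figure reproduces. It treats dropouts as contributing no information, whereas LOCF puts them back with early scores.

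**2. Formula for the LOCF estimate.** Let T and C be the mean week-4 improvements on MMDT and placebo, dT and dC the dropout shares, and f the fraction of the week-4 improvement reached at the last observation. Assume dropouts would otherwise have followed their arm's course and give no week-4 score. Then

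expected LOCF difference = T[1 − dT(1 − f)] − C[1 − dC(1 − f)].

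Two special cases follow:
- Equal dropout d: (T − C)[1 − d(1 − f)]. A true effect shrinks, and a zero effect stays zero.
- No drug effect, both arms improving by m: m(1 − f)(dC − dT). Bias needs both improvement over time and unequal dropout.

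**3. In SD units at the planned effect (0.85 SD, 20 % dropout in each arm).**

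| f | LOCF difference | Power, 29 per arm (SD held at 1) |
|---|---|---|
| 0 | 0.85 × 0.80 = 0.68 | 72 % |
| 0.25 | 0.85 × 0.85 = 0.723 | 77 % |
| 0.5 | 0.85 × 0.90 = 0.765 | 82 % |

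Power with 29 complete per arm would be 88.9 %.

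**4. In diary points.** Assumptions: linear improvement, between-patient SD 1.5, within-patient SD 1.0, and last score at week 1 or 2 with equal chance, so f = (0.25 + 0.5)/2 = 0.375 and 1 − f = 0.625. Rejection rates come from simulated t-tests with 29 per arm.

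True effect 1.5 points (T = 3.5, C = 2):

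| Dropout MMDT / placebo | Expected LOCF difference | Change | Rejection rate |
|---|---|---|---|
| 20 / 20 % | 1.5 × 0.875 = 1.31 | −12.5 % | 71 % |
| 30 / 10 % | 3.5 × 0.8125 − 2 × 0.9375 = 0.97 | −35 % | about 46 % |
| 10 / 30 % | 3.5 × 0.9375 − 2 × 0.8125 = 1.66 | about +10 % | 90 % |

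No drug effect:

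| Improvement, both arms | Dropout MMDT / placebo | Spurious difference | Type I error |
|---|---|---|---|
| 2 points | 20 / 20 % | 0 | about 5 % |
| 0.5 point | 10 / 30 % | 0.5 × 0.625 × 0.20 = 0.06 | about 5 % |
| 1 point | 15 / 25 % | 1 × 0.625 × 0.10 = 0.06 | about 5 % |
| 1 point | 10 / 30 % | 1 × 0.625 × 0.20 = 0.125 | about 5.7–5.9 % |
| 2 points | 15 / 25 % | 2 × 0.625 × 0.10 = 0.125 | about 5.6–5.9 % |
| 2 points | 10 / 30 % | 2 × 0.625 × 0.20 = 0.25 | about 8 % |
| 2 points | 5 / 35 % | 2 × 0.625 × 0.30 = 0.375 | about 11–12 % |

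**5. Standard errors.** At 2 points' improvement and 20 / 20 % dropout with no drug effect, the mean estimated standard error is 0.490 and the true sampling SD 0.493. In this model the estimate is shifted and its standard error is sound.

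**6. Laboratory values.** At 20 % dropout, 0.20 × 29 = 5.8 participants per arm would lack a week-4 sample if none is taken on stopping. With a pre-treatment value in each gap, a mean shift falls to 1 − 0.20 = 80 % of its size, if dropouts would have shifted like the rest.

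**The case against.** The strongest reply is that the damage is hypothetical. The article gives one overall dropout figure and no split by arm. With equal dropout, LOCF shrinks a true effect, which does not favour MMDT. The larger type I errors need a 2-point placebo improvement and a wide imbalance, with every dropout gone by week 2. Entry requires a run-in score of only about 2, so the lowest-scoring participants could not improve by much more than that, and the model has no floor. The trial is declared exploratory. All of this stands, and it is why the milder rows are shown and why the point is not rated higher.

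Four stronger readings are tempting, and the documents do not support them:
- **That LOCF makes the standard errors wrong.** The planned test uses one value per participant, so no false observations are added, and step 5 shows no discrepancy.
- **That LOCF biases the result in every case, or in MMDT's favour.** With no effect and equal dropout the bias is zero; otherwise its direction depends on the split.
- **That harm would go unseen.** Safety also rests on adverse reaction reports and continuous monitoring of adverse events, including blood results. Only mean laboratory comparisons could be diluted. Even that relies on reading the unrestricted LOCF sentence literally, since the article does not expressly say that laboratory values are carried forward.
- **That no sensitivity analysis exists.** An analysis plan not shown may contain one. LOCF is the only method named in this article, and no more can be said.

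The per-protocol analysis requires diary entries on 80 % of study days, so it involves little imputation. It is a selected population, however, and does not test the LOCF assumption.

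**Conclusion.** The concern holds in a conditional form. LOCF is a stated choice, and it conflicts with the plan's own expectation that benefit grows with treatment time, with 20 % dropout allowed for and one diary day enough for inclusion. With equal dropout the likely cost is an attenuated effect: about 12–13 % in the diary-point illustration, and 10–20 % across f = 0.5 to 0. With unequal dropout the estimate can move either way. Type I error then runs from near nominal under mild assumptions to 8–12 % under steep ones. The size depends on assumed trajectories, dropout timing and arm splits that the article does not give.

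The laboratory point follows from Table 1 and the unrestricted wording, and is confined to mean comparisons. This should be fixed. It does not by itself invalidate the trial, but an estimate meant to inform a larger trial should not depend on a flat course after dropout.

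**What to change.** Before unblinding:

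1. Make the primary analysis a likelihood-based mixed model on the repeated diary scores over weeks 1–4, with baseline, treatment, week and treatment-by-week, and the week-4 contrast as the estimate.
2. Add a delta-adjusted sensitivity analysis in which scores after dropout are worse than the model predicts, including different shifts by arm.
3. Keep LOCF only as a sensitivity analysis.
4. State that safety laboratory values are analysed as observed, without carrying baseline forward.

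No new participants or measurements are needed, because the daily diary already supplies the repeated scores, and the sample size can stay at 58. The cost is slightly more analysis work and a documented change in a trial that is already recruiting. The authors must also state how daily entries form each week's score. The mixed model brings its own assumption, that data are missing at random; the delta-adjusted analysis is there to probe it.

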### Participants

#### Inclusion, exclusion, and withdrawal criteria

The inclusion criteria are: (1) age between 19 and 75 years; (2) chronic cough that has lasted more than 8 weeks; (3) dry cough (sputum frequency of 5 or fewer times per day, and sputum volume less than 10 ml per day, on the basis of the Sputum Severity Evaluation Standard of the Korean Ministry of Food and Drug Safety); (4) provision of written informed consent.

The exclusion criteria are: (1) abnormal pulmonary function test (forced vital capacity, or forced expiratory volume in 1 s, < 80 % of predicted); (2) abnormal chest X-ray; (3) acute respiratory disease, including upper respiratory tract infection, during the previous 4 weeks; (4) chronic pulmonary diseases (COPD, idiopathic pulmonary fibrosis, bronchiectasis, etc.) during the previous 2 years; (5) diagnosis of malignant tumor during the previous 5 years; (6) history of smoking (≥20 packs [400 cigarettes] during the participants’ lifetime); (7) treatment taking an angiotensin-converting-enzyme inhibitor at present or during the previous 4 months; (8) current or the precious 2-week use of antitussive drugs, glucocorticoids, leukotriene receptor antagonists, anticholinergic drugs, long-acting β2 agonists or any herbal medication; (9) antihistamine treatment during the previous 3 days; (10) aspartate aminotransferase (AST) or alanine aminotransferase (ALT) levels at least twofold higher than the upper normal limit, or a serum creatinine levels at least 1.2-fold the upper normal limit; (11) a mean cough diary score of less than 2 during the 1-week run-in period; (12) fewer than 10 entries in the cough diary during the 1-week run-in period; (13) pregnancy or breastfeeding; (14) illiteracy or cognitive impairment; (15) unsuitability as judged by the investigators.

The rejection and withdrawal criteria are: (1) treatment that might influence the results of the trial without the agreement of an investigator; (2) use of forbidden drugs, such as antitussives, glucocorticoids, leukotriene receptor antagonists, anticholinergics, and long-acting β2 agonists; (3) participants not following the protocol, or taking < 80 % of the prescribed doses; (4) a serious adverse event (SAE) during the trial; (5) voluntary withdrawal from the trial; (6) unsuitability as judged by the investigators.

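### The primary test ignores the recorded baseline diary score and lets a normality check choose between a t-test and a rank test: valid on average, but it gives up precision that baseline adjustment would recover at almost no cost

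*Protocol article*

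**What the plan says.** All references are to the protocol article.

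- **Outcome and baseline (Primary outcomes).** "The primary outcome is the cough diary score at week 4", so the endpoint is a final value and not a change. The same section defines a baseline: "The cough diary score on the last day of the 1-week run-in period will be taken as the baseline score".
- **Run-in data (Inclusion, exclusion, and withdrawal criteria).** One ground for exclusion is "fewer than 10 entries in the cough diary during the 1-week run-in period". Another is a mean run-in score below 2.
- **Primary test (Statistical analysis).** A t-test is to "be used to compare the two groups in terms of the primary outcome (mean cough diary score at week 4". This applies only if the data pass a check of normality. The fallback is stated next: "Otherwise, the Mann–Whitney *U*-test will be used". VAS, LCQ and biomarkers are to be analysed by the same methods, and Table 1 schedules a baseline measurement for each of them.
- **Covariates (Statistical analysis).** Adjustment appears only for the associations between responder status and pattern, which "will be estimated using a logistic regression model, which will be adjusted for covariates".
- **Randomization and Concealment.** Blocks of 4, 1:1. No stratification by baseline severity is stated.

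**The concern.** As stated, neither the allocation nor the primary analysis takes account of how severe the cough was at entry. In a trial of 29 per arm, the arms can differ noticeably at baseline by chance, and part of that difference reappears at week 4. A baseline that predicts the outcome also explains part of the week-4 variance, and the unadjusted test leaves that part in the error term.

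The second issue is the rule for choosing the test. A t-test concerns a difference in mean score and Mann–Whitney concerns a shift in ranks. If the trial data decide between them, the tested quantity is not fixed in advance. If the rank test is selected, the plan names no effect in score points. The Discussion presents this trial as the basis for a larger one, which would need a mean difference and an SD.

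The article commits to this test and this rule, so the point is not a detail left to an unseen analysis plan.

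**Working it through.** **Inputs from the article (Sample size calculation; Statistical analysis):** two-sided α 0.05, power 0.80, source effect size 0.699, adjusted effect size 0.85, dropout 20%, total 58 (29 per arm).

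**Assumption:** the correlation r between baseline and week-4 score is not given. It is taken as 0.3, 0.5 or 0.7.

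**1. The plan's own figure.** For the two-sample t-test, the noncentrality is d·√(n/2) with 2n − 2 degrees of freedom. With d = 0.85 and n = 23, it is 0.85 × √11.5 = 2.88 and power is 0.805, so 23 per arm suffices. Then 23/0.8 = 28.75, rounded up to 29 per arm, or 58 in total. The stated sample size reproduces, and it rests on the unadjusted test. With d = 0.699 and n = 23, the noncentrality is 2.37 and power is 0.64.

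**2. Chance imbalance at 23 per arm.** The SD of the baseline difference is √(2/23) = 0.29 SD units, and its 95% limit is 1.96 × 0.295 = 0.58. The expected shift in the unadjusted week-4 difference is r times the imbalance. At the 95% limit this is 0.17, 0.29 or 0.40 SD for r = 0.3, 0.5 or 0.7, against a target effect of 0.85 SD.

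**3. Gain from ANCOVA at 23 per arm.** The residual variance is multiplied by 1 − r², the effect size becomes d/√(1 − r²), and one degree of freedom is lost.

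| r | 1 − r² | Power, d = 0.85 | Power, d = 0.699 | 46 evaluable worth 46/(1 − r²) |
|---|---|---|---|---|
| Unadjusted | 1 | 0.80 | 0.64 | 46 |
| 0.3 | 0.91 | 0.84 | 0.68 | 51 |
| 0.5 | 0.75 | 0.90 | 0.76 | 61 |
| 0.7 | 0.51 | 0.98 | 0.90 | 90 |

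**4. If LOCF keeps all 29 per arm** (taking d as unchanged). At d = 0.85, unadjusted power is 0.89 and ANCOVA gives 0.92, 0.96 or 0.99.

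**5. Type I error, by simulation** (20,000 trials per setting, 23 per arm). The unadjusted t-test holds 0.05 overall. Among trials whose baseline difference exceeds one standard error, its type I error is 0.07, 0.09 or 0.12 for r = 0.3, 0.5 or 0.7. ANCOVA stays at about 0.05 in the same trials.

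**6. The normality rule, by simulation.** This used 4,000 trials with identical arms of 23, skewed scores rounded to 0–10, and a Shapiro–Wilk check in each arm. The overall type I error was 0.053. The Monte Carlo standard error is √(0.05 × 0.95/4000) = 0.003, so this is compatible with 0.05.

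**The case against.** The strongest defence is that nothing here is miscalculated or contradictory. Comparing final scores without adjustment in a 1:1 randomized trial is unbiased over randomization, holds its type I error, and is the analysis for which the 58 participants were calculated. The trial also calls itself exploratory. All of this stands. It makes the point one of efficiency and prespecification, not of error.

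The size of the gain is uncertain. A single-day baseline and a sample restricted to run-in means of at least 2 both tend to lower r, and at r = 0.3 the gain is only about 4 points of power. If LOCF keeps nearly everyone, the gain at the design effect is about 3 to 10 points, from a starting power of 0.89. This also stands, and it is why a range is shown.

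Four stronger readings are tempting and are not supported:

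- **That the normality rule inflates false positives.** The illustrative simulation shows no material inflation. Its fault is that the tested quantity is not fixed.
- **That normality will be checked on the wrong quantity.** The article refers only to the assumption of normality and does not say what is checked. Checking within groups would be checking residuals.
- **That a baseline imbalance passes in full into the week-4 result.** It passes multiplied by r.
- **That every participant has the defined baseline.** Eligibility secures at least 10 run-in entries, not an entry on the last day. What every eligible participant has is a run-in mean.

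**Conclusion.** The point holds as a recommended improvement. The planned primary test is valid on average and the sample size is not wrong. A reader might infer that the result would be biased or the trial underpowered on its own terms, but the documents support neither.

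What is lost is precision, and protection against a chance imbalance in the particular trial that is run. With 23 evaluable per arm, adjustment is worth about 4, 10 or 17 points of power at d = 0.85, and about 4, 12 or 26 points at d = 0.699, for r = 0.3, 0.5 or 0.7. The second set matters because 0.85 was reached by raising the source value of 0.699, at which the unadjusted test has power of only 0.64. These sizes rest on the assumed r and on a linear relation between baseline and week-4 score. The direction of the gain does not depend on r, provided that it is not close to zero.

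The normality rule is a separate, smaller defect: the primary comparison should be fixed before the data are seen.

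**What to change.** Prespecify one primary analysis: ANCOVA of the week-4 diary score with treatment and baseline diary score as terms, reporting the adjusted difference in score points with its 95% CI.

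- **Covariate.** Use each participant's mean run-in score. Every eligible participant has it, and it is more reliable than one day's score. The baseline definition in Primary outcomes needs to be changed to match.
- **Normality rule.** Delete it, and keep Mann–Whitney as a sensitivity analysis.
- **VAS and LCQ.** Use the same model, each with its own baseline.
- **Biomarkers.** Adjust for baseline after a suitable transformation, such as the log, where values are skewed, as may be the case for IgE and cytokines. A rank-based method is an alternative. ANCOVA on untransformed values should not be applied to them across the board.

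The cost is one degree of freedom and a change of wording in the analysis plan, made before unblinding. No further participants, measurements or software are needed, since SPSS already fits the model.

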### Safety outcomes

Safety will be investigated using adverse reaction reports and clinical laboratory tests; namely, liver function tests (AST, ALT, alkaline phosphatase [ALP], total bilirubin [TB], and γ-glutamyltranspeptidase [GGT] levels), renal function tests (blood urea nitrogen [BUN] and creatinine levels), and serum sodium and potassium levels. All women of childbearing age will also undergo human chorionic gonadotropin testing.

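### The only laboratory-specific safety analysis stated is a two-group significance test, which at about 29 per arm has very low power to show one to three large individual rises

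*Protocol article*

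**What the plan says.** Under Statistical analysis, the protocol article first sets the test for the primary outcome. A t-test will "be used to compare the two groups in terms of the primary outcome" when normality is satisfied, and the Mann-Whitney test will be used otherwise. It then extends this rule: "safety tests (AST, ALT, ALP, TB, GGT, BUN, creatinine, sodium or potassium levels), and biomarkers will be analyzed using the same statistical methods". On significance it says: "The level of significance will be set at a two-sided P value of 0.05". The same section also promises descriptive statistics for continuous variables in general.

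The Safety outcomes section names two sources of evidence: "Safety will be investigated using adverse reaction reports and clinical laboratory tests". Adverse event reporting describes continuous monitoring, with decisions that draw on signs and on blood test results. Numerical laboratory limits appear only among the exclusion criteria, for example "alanine aminotransferase (ALT) levels at least twofold higher than the upper normal limit", with a corresponding creatinine limit of 1.2 times. They govern entry. Table 1 schedules safety tests at screening, visit 1 and week 4.

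Safety is part of the Objective, and the Discussion says the trial aims to demonstrate it.

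**The concern.** In a group of 29 treated people, liver or kidney toxicity would plausibly appear as one, two or three participants with marked rises while everyone else stays near baseline. A two-group test asks whether the arms differ overall. The Mann-Whitney test uses ranks, so once a value is the highest in the trial it makes no difference how high it is.

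The result the article fixes for these variables would therefore usually be non-significant, whether or not a few MMDT participants had large rises. Safety is one of the two things the trial sets out to assess, so such a p-value could lend support that it cannot carry.

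**Working it through.** **1. The sample size, and what it was sized for.** Inputs from Sample size calculation: "α = 0.05, 1-β = 0.8, 2-tailed test", "this resulted in an adjusted effect size of 0.85", and "Assuming a 20 % dropout rate, and an allocation ratio of 1". A two-sample t-test (noncentral t) with d = 0.85 needs 23 per arm (power 0.805). Then 23 / (1 − 0.20) = 28.75, rounded up to 29 per arm, 58 in total. The article's figure is reproduced. It was sized for the cough diary only and gives no assurance for laboratory values.

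**2. Which branch of the rule applies.** Assumption, not from the documents: ALT is normal with mean 22 and SD 8 U/L in both arms, 29 per arm, and k of the MMDT values are set to 200 U/L. The article names no normality check. With Shapiro-Wilk (also an assumption), normality was rejected in 100 % of simulated trials for k = 1, 2 and 3. The rule therefore leads to Mann-Whitney.

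**3. Chance of p < 0.05 with Mann-Whitney, 29 per arm, by simulation.**

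| MMDT participants at 200 U/L | Trials with p < 0.05 |
|---|---|
| 0 | about 5 % |
| 1 | about 5 % |
| 2 | about 6 % |
| 3 | about 9 % |

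**4. Check by hand.** Under no difference, the SD of U is √(29 × 29 × 59 / 12) = 64.3, so rejection needs a deviation of 1.96 × 64.3 = 126.0. Each value above all others adds 29 − 14.5 = 14.5 to the expected U. With k such values fixed, the SD of U is √((29 − k) × 29 × (59 − k) / 12).

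- k = 1: shift 14.5, SD 62.6. Upper tail beyond (126.0 − 14.5) / 62.6 = 1.78 is 3.8 %; lower tail is 1.2 %. Total 5.0 %.
- k = 2: shift 29.0, SD 61.0. Upper tail beyond 1.59 is 5.6 %; lower tail is 0.6 %. Total about 6.1 %.
- k = 3: shift 43.5, SD 59.3. Upper tail beyond 1.39 is 8.2 %; lower tail is 0.2 %. Total 8.4 %.

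These agree with the simulation. They do not use the assumed ALT mean and SD, only that the raised values are the highest in the trial.

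**5. Sensitivity.** With a lognormal ALT instead (assumed median 20, log-SD 0.4, upper limit 40) and rises to 3, 5 or 10 times the limit, Mann-Whitney rejects in about 5 %, 6 % and 8 % for k = 1, 2 and 3 at 29 per arm. If a t-test were used despite the outliers, its highest rejection rate in any of these settings was about 20 % (k = 3, rise to 3 times the limit; 19.3 % at 29 per arm, 20.5 % at 23 per arm).

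**6. What counts per participant would give.** For 0 of 29, the exact two-sided 95 % upper limit is 1 − 0.025^(1/29) = 11.9 %; for 0 of 23 it is 1 − 0.025^(1/23) = 14.8 %. Fisher's exact test at 29 per arm gives p = 1.0 for 1 vs 0, 0.49 for 2 vs 0, 0.24 for 3 vs 0, 0.052 for 5 vs 0 and 0.023 for 6 vs 0.

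**The case against.** Four points can be made for the plan.

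- **The laboratory test is not the only safety evidence.** Adverse reaction reports stand beside it, and blood results feed adverse-event decisions for individual participants, so a large rise can surface there. This stands and limits the concern. The safeguard is partial: Table 1 schedules one safety test after treatment starts, and the article leaves it to judgement whether a rise without symptoms is recorded. That the article gives no numerical trigger is not held against it, since the full protocol may do so.
- **No section says that a non-significant laboratory test means the drug is safe.** This also stands. A reader might infer from the Discussion that non-significance would be reported as safety, but the article does not state that rule, and it calls the trial exploratory. It would likewise go too far to say that laboratory safety is judged only by comparing means, or that the test cannot detect rises. The applicable branch compares ranks, and its power is very low, not zero. That an outlier inflates the SD and weakens the t-test is true, but under the normality rule that test would not be used here.
- **Shift tables and threshold counts may be in an analysis plan that is not shown.** Accepted: their absence is not the point. The point is that the article fixes a significance test for these variables.
- **Counts are no more powerful.** Correct: 3 vs 0 gives p = 0.24, and the 11.9 % limit is set by the sample size under any analysis. What counts add is that they show the cases and the uncertainty, which a p-value from a rank test hides.

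**Conclusion.** The concern holds in a limited form. The stated laboratory method is poorly matched to the pattern of harm most relevant at this sample size. With one, two or three of 29 MMDT participants showing a large rise, it would reject in about 5 %, 6 % and 9 % of trials, against about 5 % with no rises. For one or two cases that is at or close to the false-positive rate.

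The figures rest on full arms of 29, no rises on placebo, raised values above all others, and a normality check that detects them. The ALT distribution is assumed, but the Mann-Whitney result hardly depends on it.

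The article does not commit the sponsor to reading non-significance as safety, and adverse-event monitoring offers a second route. What follows is narrower: a non-significant laboratory comparison should carry no weight towards the aim of demonstrating safety, and the main laboratory summary should be one that displays individual cases.

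**What to change.** In Statistical analysis, take the laboratory safety variables out of the sentence that gives them the primary-outcome test, and state instead:

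- The main laboratory safety summary is the number of participants per arm with a post-baseline value beyond predefined reporting limits, with exact 95 % confidence intervals. The limits could be the normal range and, for AST, ALT and creatinine, the multiples already used in the exclusion criteria. They would serve as analysis cut-offs only, not as clinical rules.
- Shift tables from baseline to week 4 are given by arm and presented alongside the adverse events.
- Means or medians are descriptive, and no safety inference is drawn from p > 0.05.

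This needs no new data, only changed wording and a few more tables. The drawback is a less favourable safety statement, because the intervals will be wide: even with no cases among 29, the upper limit is 11.9 %.
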